### 11.2 MINIMUM CLINICALLY IMPORTANT DIFFERENCE (MCID)

#### 11.2.1 Suicide Attempts

Suicide Attempts are one of the leading causes of morbidity in the US health care system with more than 1,400,000 attempts in 2018 and are the best predictors of further suicide attempts and death from suicide. The ability to prevent even just one suicide attempt reflects the ability to 1) prevent a tragedy that affects not just the individual, but also their families and communities and 2) potentially reduce costs of healthcare system utilization related to suicide attempts with a relatively low-cost intervention. **There are currently NO FDA approved products that are suitable for a broad audience of adults.** Given the importance of suicide attempts and the binary nature of attempts any statistically significant difference between the control and treatment arms would be meaningful for clinicians and their patients. While studies using face-to-face implementation of the techniques used by Aviva have shown more than 40% reduction in incidence of suicide attempts relative to a control condition (Brown et al., 2005, Bryan et al., 2017, Rudd et al., 2015) we do not feel patients should be kept from an intervention that shows a lower, but significant, chance of decreasing an attempt. Given the lack of any FDA approved or cleared

products available, any statistically significant result at the 0.025 level of significance (one-sided) is clinically important and has the potential to have meaningful impact both at the societal and individual level, particularly in this moderately sized clinical study. Statistical significance is important at this stage because a suicide attempt is a clinically important life event. The clinical significance of the findings of studies using our proposed techniques is evidenced by the adoption of these techniques by the Joint Commission (The Joint Commission, 2016) and the U.S. Department of Veterans Affairs (U.S. Department of Veterans Affairs, 2008).

### **11.2.2 Suicidal Ideation**

Effect size will be used as a measure of minimally clinically significant difference (MCID). This study has been designed to detect an effect size of 0.50 for suicidal ideation (assessed through the SSI), which is both a moderate effect size and a clinically significant amount. To calculate this expected effect size, the standard deviations presented in research that used the same suicide prevention techniques proposed to implement with Aviva (Bryan et al. 2017) were reviewed. The clinical significance of the findings of studies using the proposed techniques (Brown et al., 2005, Bryan et al., 2017, Rudd et al., 2015) is evidenced by the adoption of these techniques by the Joint Commission (The Joint Commission, 2016) and the U.S. Department of Veterans Affairs (U.S. Department of Veterans Affairs, 2008).

To support the effectiveness of Aviva for SI, it will be beneficial to demonstrate what constitutes a clinically meaningful within-patient change in scores (i.e., improvement threshold), from the patient perspective, in addition to an MCID across all patients. To estimate a clinically meaningful within-patient change, the following scales will be included to support a clinically meaningful within-patient change analysis (an improvement score of 1 unit on the CGI-C scale), and aim to achieve statistically significant and clinically meaningful differences in a responder analysis between the treatment and control groups for the two scales identified below:

- Clinician Global Impression of Severity (CGI-S) administered at baseline, 24 weeks and at study end
- Clinician Global Impression of Change (CGI-C) administered at 24 weeks and at study end

## **11.3 ANALYSIS SETS, SENSITIVITY ANALYSES AND SUBGROUP ANALYSIS**

The analysis sets will be:

1. ITT: all participants randomized into our study.
2. Per-protocol population (PP): The PP population will include all ITT participants with no major protocol deviations. Major protocol deviations are defined as follow:
  - a. Participant did not complete informed consent procedures
  - b. Participant is not randomly assigned to a treatment condition
  - c. Participant is enrolled in the wrong treatment arm (i.e., a different treatment arm than the one to which they were randomly assigned)
  - d. Enrolled participant did not meet eligibility criteria
  - e. Participant did not complete onboarding. Onboarding entails downloading the app and completing session 1
  - f. Participant is unblinded due to staff error
3. The Safety Analysis population set consists of all randomized patients that have begun treatment, as defined by completion of the onboarding process. This set will be used for all safety analyses using treatment actually received. Since onboarding occurs prior to discharge, it is assumed that both populations will be identical.

The sensitivity analyses will proceed in the following manner: the primary analysis will be repeated in the per-protocol population and the Cox proportional hazards model will be carried out on the ITT population to investigate the robustness of the finding for suicide attempt in the presence of potentially important factors such as sex, race/ethnicity, and site. The ITT will be used for the primary and secondary endpoint analysis either here or in the sections above where each is discussed. Associated Wald tests will be conducted using a significance level of .05 (2-sided) to test the null hypothesis that the two time-to-event distributions are the same for the Aviva and sham groups at any time point. We will conduct subgroup analysis based on the stratification factors used in our randomization (sex, race/ethnicity and previous suicide attempt history [i.e., whether participants had no suicide attempts, a single attempt or multiple suicide attempts] and investigative site). We will include sex, race/ethnicity because differences in rates (or increases in rates) have been observed for each. Regarding sex, the age adjusted suicide death rate for males (22.79 per 100,000) is higher than the rate for females (6.18 per 100,000; CDC, 2020). For race/ethnicity, American Indian/Alaska Native adults are at highest risk for past-year suicide attempts, followed by Black and Hispanic adults (CDC, 2020). Lastly, while all efforts will be made to standardize procedures across sites, it is possible that site differences may emerge. Thus, we will examine whether there are any treatment differences based on sites. Lastly, previous suicide attempt history is a strong predictor of future suicide attempts.

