## **2.2 AVIVA**

### **2.2.1 App Overview**

Aviva is designed to be user friendly and for use by patients that does not require guidance from a qualified health professional after the initial onboarding session. Patient progression through the 12 sessions of the Aviva treatment platform is divided into phases. Consistent with the procedures presented in the BCBT and CT-SP protocols, Aviva includes an early phase that entails assessment and development of a plan for keeping participants safe (phase 1), an intermediate phase that involves teaching suicide specific cognitive and behavioral skills (phase 2) and a final phase that summarizes specific skills learned to prevent relapse of suicidal thinking and suicide attempts.

The three phases are executed via 12 sessions (see Table 2). Participants complete an initial onboarding session that includes planning for safety and identification of warning signs from the most recent suicide attempt. After completion of the initial onboarding session, participants complete several skills training sessions, each designed to take 10-20 minutes to complete. For a description of the rationale for the sessions, see the *Overview of the Product Development* section. Note that the design and development of Aviva is ongoing.

Table 2. Intervention phases from proven cognitive behavioral protocols (BCBT/CT-SP) that are included in Aviva

| Phase                                             | BCBT
(Rudd et al., 2015) | CT-SP
(Brown et al., 2005) | Aviva |
|---------------------------------------------------|-----------------------------|-------------------------------|-------|
| Phase 1
(Planning for Safety)                  | X                           | X                             | X     |
| Phase 2
(Cognitive Behavioral Skills Training) | X                           | X                             | X     |
| Phase 3
(Relapse Prevention)                   | X                           | X                             | X     |

Table 3. Aviva Sessions and Duration

| Session Topic                                     | App Time (min.) |
|---------------------------------------------------|-----------------|
| Onboarding                                        | 20 – 45         |
| Reasons for Living/Hope kit                       | 10 – 20         |
| Get Going (Activity Planning/Behavior Activation) | 10 – 20         |
| Relaxation and Mindfulness                        | 10 – 20         |

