## 7.4 PARTICIPANT ENROLLMENT

To preserve participant blinding, participants will be informed that they will be assigned to "one of two digital interventions." Participants will be informed that both interventions include some combination of supportive listening, education about crisis services, software services and referrals to treatment services. Once the patient agrees to participate, the PI will review the patient's medical history and psychological evaluation with the patient and gather additional information to determine whether the patient meets eligibility criteria. The site PI will obtain informed consent from participants using procedures that will be Internal Review Board (IRB) approved. After informed consent is given, research therapists will administer a structured clinical interview focused on suicide attempt history. Upon completion, the research therapist will execute a randomization procedure and the participant will be randomized to the Aviva + TAU or sham +

TAU group (See Section 7.5). Following randomization, participants in both groups will receive an access (SMS) link and instructions on how to install the Aviva or sham apps on their phone. The app is to be downloaded before the end of the study visit.

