#### 9.8 REPORTING PERIOD

In this study, all adverse events are collected starting at the time informed consent has been signed. AEs are collected until the last study visit and exit from the study.

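### Section 11.3 treats completing onboarding as the start of treatment, so a participant who starts session 1 and stops is exposed to the app but left out of the safety set

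*Protocol*

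**What the plan says.** Section 11.3 of the protocol defines the safety analysis set as "all randomized patients that have begun treatment, as defined by completion of the onboarding process". Its scope is wide: "This set will be used for all safety analyses using treatment actually received".

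The meaning of completion is given a few lines earlier, in criterion 2e for major protocol deviations: "Participant did not complete onboarding. Onboarding entails downloading the app and completing session 1". Criterion 2e removes such participants from the per-protocol set; they stay in the ITT set, which is everyone randomized.

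The section closes the safety definition by reasoning that onboarding takes place before discharge, so the two populations can be assumed to coincide. It does not say which two; the natural reading is the safety set and all randomized participants.

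Three other places bear on the point:
- Section 2.2.1 describes an "initial onboarding session that includes planning for safety and identification of warning signs from the most recent suicide attempt". Table 3 gives it 20 to 45 minutes, against 10 to 20 for every other session.
- Section 7.4 says what must be done on the day: "The app is to be downloaded before the end of the study visit".
- Section 9.8 says that "all adverse events are collected starting at the time informed consent has been signed".

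**The concern.** A safety set should contain everyone who was exposed. Here the set is labelled by the start of treatment but defined by the end of the first session. Between those two moments lies a session of up to 45 minutes, with people recently admitted for a suicide attempt or for ideation with intent. Someone who becomes distressed and stops has been exposed and may have an adverse event on record, but is not in the set.

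Membership therefore depends on something that happens after randomization and may itself reflect how well the app is tolerated. Section 3.2.3 promises an assessment of adverse events in both conditions and names worsening of existing symptoms as the main risk. Section 2.1.2 calls the trial a pivotal effectiveness and safety study. The between-arm adverse event tables should not drop participants for a reason that could be the event of interest.

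**Working it through.** The protocol gives no figure to reproduce here. The check is a reading of its own passages side by side, followed by arithmetic on assumed rates.

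**Does the definition exclude exposed participants?**
1. Safety set: randomized and onboarding completed (11.3).
2. Onboarding completed: app downloaded and session 1 finished (11.3, criterion 2e).
3. Session 1 delivers app content from its beginning (2.2.1, Table 3), so exposure precedes completion.
4. A participant who starts session 1 and does not finish it meets 3 but not 2, and is therefore outside 1.
5. Adverse events are collected from consent (9.2, 9.8), so this participant's events are recorded but fall outside the set used for safety analyses.

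**Does the protocol rule such participants out?**
- Section 11.3 assumes that the populations coincide. Criterion 2e, "Participant did not complete onboarding", is written for participants who break that assumption.
- Section 7.4 requires a download before the visit ends. Section 7.5 has staff confirm the download and help a participant in difficulty to begin onboarding. Neither requires session 1 to be finished.
- Section 8.2 recognises that participants may simply stop using the app without telling anyone.

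Completion is expected but not guaranteed.

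**How many could be left out?** The documents give no non-completion rate, so the rates below are assumptions. Left out = 391 × rate.

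| Assumed rate | Left out | Safety set |
|---|---|---|
| 0% | 0 | 391 |
| 1% | 4 | 387 |
| 2% | 8 | 383 |
| 5% | 20 | 371 |
| 10% | 39 | 352 |

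**What could it do to an arm's adverse event rate?** Take the Aviva arm, n = 196 (11.1.4). Let k participants stop session 1, all of them because of an adverse event, which is the extreme case. Let 10 others have an adverse event (an assumed count).

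Rate among all randomized = (10 + k)/196. Rate in the safety set = 10/(196 − k).

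- k = 0: both are 10/196, so there is no difference.
- k = 2 (1%): 12/196 = 6.1% against 10/194 = 5.2%.
- k = 10 (5%): 20/196 = 10.2% against 10/186 = 5.4%.

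If those who stop have events at the same rate as everyone else, the rate is unchanged on average and only the counts fall. The distortion comes from stopping that is linked to harm.

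**The case against.** The strongest reply is that non-completion should be rare and that the important events are covered elsewhere. Much of this stands.

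- Table 1 puts onboarding at the in-person Day 1 visit. Section 4.2.2 has Aviva participants complete it with their clinician while preparing for discharge, section 2.3.1 has a clinician available during setup, and Table B1 marks it as the only clinician-assisted session. Completion is the planned norm.
- Section 3.2.3 names increased ideation and suicide attempts as the primary anticipated events. Section 11.3 uses the ITT set for the primary endpoint (attempts) and the secondary endpoint (SSI).
- Safety events and SAEs go to the DSMB (9.9), which reviews all suicide attempts (11.5). Section 9.2 also lists SAEs, deaths and UADEs separately.

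These provisions protect monitoring and the effectiveness analyses. They do not restore excluded participants to the comparative adverse event tables.

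A reader might infer three stronger things, which the documents do not support.

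*That harmed participants vanish from every evaluation of safety.* They do not, for the reasons just given. What is affected is the set of analyses run on the safety set.

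*That the comparison leans toward showing no harm because session 1 differs by arm.* Section 2.2.1 places skills training after onboarding. Table 4 gives both arms a safety plan that documents warning signs, and section 4.2.1 matches the sham app to Aviva in number of sessions, frequency and duration. The sham's first session is not described. Clinician-assisted onboarding is described for Aviva with no counterpart stated for sham, so completion could differ, but its direction is unknown.

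*That losing 1 or 2 of the 15 Aviva attempts expected in Attachment C understates that arm by 7 to 13% (1/15 and 2/15).* This ignores the shrinking denominator. Against 15/196 = 7.7%, losing 1 event and 4 people gives 14/192 = 7.3%, about 5% lower in relative terms. Losing 2 events and 20 people gives 13/176 = 7.4%, about 3.5% lower. Losing 1 event and 20 people gives 14/176 = 8.0%, which is higher. At average risk, 2 to 10% non-completion removes only 0.3 to 1.5 of the 15 events. Attempts are in any case counted in full in the ITT analysis.

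**Conclusion.** The point holds as a defect in a rule the protocol itself fixes. The safety set is conditioned on finishing session 1, a post-randomization event that may reflect tolerability, and the assumption offered in its defence is undercut by criterion 2e in the same section.

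The consequence is confined to the safety-set analyses, chiefly the between-arm adverse event tables. Its size depends on a non-completion rate that the documents do not give: nobody is lost at 0%, and 39 of 391 at an assumed 10%. Any distortion of rates also depends on how far stopping is linked to adverse events, and neither its size nor its direction between arms can be derived.

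It is worth correcting because the current wording has no advantage. If everyone completes onboarding, a wider set is the same set; if some do not, the current rule drops exposed participants.

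**What to change.** In section 11.3:
- Define the safety set as all randomized participants or, if an exposure-based set is preferred, all randomized participants who downloaded or opened either app.
- Analyse by the app actually received, and as randomized where neither was received.
- Delete the clause that defines the start of treatment by completion of onboarding, and the sentence assuming that the populations are identical.
- Keep onboarding completion as per-protocol criterion 2e only.

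The cost is a short edit to one section. Adverse events are already collected from consent, randomization is recorded and staff confirm the download, so no new data, visits or participants are needed. The primary and secondary endpoint analyses are unaffected.

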#### 11.4 ADDITIONAL CONSIDERATIONS

**Poolability analysis:** Descriptive statistics will be provided by site to present an overall study summary. We will remove any sites with <10% of patients from the poolability analysis. Poolability analysis will examine site as a covariate in a Cox proportional hazards model for the primary endpoint. The site effect will be evaluated at a 0.15 level of significance. Due to the relatively small rate of expected events, we feel this is more appropriate than a site-by-treatment interaction term analysis. A similar analysis will be repeated to assess poolability of race, sex and age. Sites with fewer than 5 subjects from the poolability analysis.

**Sites:** To prevent the scenario of one site dominating the study, we will cap enrollment at 36% of the total enrollment at any one site in any one geographic region. We have based the proportion on the 4 sites that are currently identified as potential participating sites. At present, current patient flow at the 4 sites suggests it is not likely that more than 1 site would reach this threshold. Should we identify an additional 4 sites (bringing the total to 8), we will reduce the percentage to 20%. Center will be used as a nuisance factor in the analyses.

**Additional time points:** While we are primarily interested in outcomes at 104 weeks, at the conclusion of the study, additional time points will be investigated.

Prior to the start of the study, we will determine the subject and study level primary outcome data elements that can be reported from all participating sites. We will collect (and confirm) information about the data elements that can be reported from all participating sites in a systematic way through a Site Assessment Questionnaire and Site Qualification Visits. Formal training for the sites will be conducted at Site Initiation Visits.

Uniform methods for collecting safety and primary outcome data will be in place across each site. We will ensure implementation of these methods through the site selection process, training of staff and additional data collection procedures for participants who drop out or are lost to follow-up.

#### Site selection and evaluation

The site selection process will ensure that each site can provide the required safety and primary outcome data. Specifically, we will evaluate whether the site has appropriate technical capabilities and personnel training to ensure proper capture of data.

1. Identification of Sites: We will identify suitable clinical trial sites through a variety of sources (e.g., professional referrals, literature review and the Clinicaltrials.gov website).
2. Feasibility Assessment Questionnaire: Each site will complete a feasibility assessment questionnaire. The questionnaire was specifically designed for this study and will allow Oui to gather specific information on the site staff qualifications and experience as well as gain an initial understanding of the site set up and access for the monitor as well as an idea of the patient volume. Based on the responses to the Feasibility Assessment Questionnaire, the sites will be selected for Site Qualification Visit.
3. Site Qualification Visit: The Site Qualification Visit will be conducted either by web meeting or in person as is allowed by the site and current Covid conditions. If conducted by web meeting, a video tour of the facility will be requested. If a video tour cannot be conducted, the sponsor will request pictures of the facility. The Qualification Visit will be conducted by the study sponsor or designee. The visit will include a meeting with the proposed PI and Study Coordinator as well as any other relevant site staff. During the visit, the Sponsor or designee will obtain information on the IRB and predicted timelines, the contract process, the subject population, the staff resources available, as well as assess the sites interest in conducting the study.
4. Site Initiation Visit and Ongoing Monitoring: Site initiation visits and ongoing monitoring will ensure that the sites are conducting the study in a manner that ensures subject safety and protocol compliance and are able (and continue) to abide by the uniform methods for collecting safety and primary outcome data.

#### Staff training at study initiation

1. Trained/Designated Staff: Each site will have designated research staff who will be trained to collect the study outcomes.
2. Clear Definitions and Electronic Data Capture: We will use a structured method for obtaining all study outcomes. For variables assessed, there will be clear definitions. Staff will receive training in how to apply those definitions and record them in the study electronic data capture (EDC) system.

